Participating communities, stratified by size of community (ie, number of children in the sample frame) and baseline dental caries experience, will be randomly assigned using a computer-generated block randomized list into immediate (test group) or delayed intervention (control group, given standard care) by a central study coordinator. We will select communities for recruitment based on available information on community population from various sources (eg, Community CEOs, the WA Country Health Service, Australian Bureau of Statistics). Communities will also be far enough apart to minimize contamination of test and control (at least 50 km). We will invite participation from communities with at least 100 people to ensure likelihood of recruiting at least 15 children in the age group of interest. We will stratify the communities on size of population and dental caries experience (high vs low; data obtained at baseline examination). Parents of all children of eligible age will be provided with information and consent forms and a questionnaire to complete (Aboriginal research assistants will explain the study to the parents and help parents complete the questionnaires). After receipt of signed consent, participants in the randomized study will be contacted for a baseline clinical examination by a calibrated examiner. After baseline examination, all participants will be contacted by the trial coordinator and appointments arranged for those allocated into the early treatment group. Test group participants will subsequently be contacted and appropriate appointments coordinated to be seen at the local SDS clinics or field clinic settings for treatment. Control group participants will be provided with standard preventive care by the Aboriginal Health Workers and managed for treatment as per standard procedures.

Study participants will be reviewed after 12 months from baseline and will undergo a clinical examination and complete a follow-up questionnaire. Figure 1 shows the study’s participant flow chart.

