### Measures

Researchers will help the parents/caregivers complete a baseline questionnaire collecting information on COHRQoL using the Early Childhood Oral Health Impact Scale (ECOHIS) for children ≤6 years old [28]. The scale has been evaluated for Australian children and found to have acceptable reliability and validity [29]. We will also collect parent fear levels using the Index of Dental Fear and Anxiety [30] and child dental fear as reported by the parents as well as self-report by children ≥3 years old using the faces scale [31]. Changes in health utility will be evaluated using the generic Child Health Utility 9D Index (CHU_9D) [32], the Euroqol 5D Youth (EQ-5D-Y), and the new oral health specific utility scale planned to be developed in this study. The ECOHIS has been used successfully among Australian Aboriginal population by author LJ in her National Health and Medical Research Council (NHMRC)‒supported research on pregnant Aboriginal women, while the other measures have been used among disadvantaged populations. We will also evaluate the validity of the questionnaires used among this population.

Participant involvement in the proposed study is shown in Table 1. Both test and control groups will complete the same questionnaire on COHRQoL, child dental fear, the CHU_9D, and the EQ-5D-Y, one month after treatment. The test and control groups will also complete the childhood oral health‒related questionnaire and the CHU_9D and the EQ-5D-Y, at the one-month posttreatment, but anchoring their responses to what their child’s oral health was like before the treatment (“Then-test”) to evaluate the possible effects of response shift [33]. Questionnaires on COHRQoL and parent/child fear and anxiety will again be collected at the 12-month follow-up.

We anticipate the clinical examination to take about 10 minutes, and completion of the questionnaire about 30 minutes. ART-based treatment times will vary depending on the extent of treatment required. Treatments may involve multiple appointments, usually about 20 minutes at each appointment. A sample of study participants will be invited to focus group interviews, which will take approximately 1 hour per group.

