All participants will also be clinically examined at the 12-month follow-up, by a “blind” calibrated examiner to evaluate their oral health status. Effectiveness will be assessed by the number of teeth treated, dental caries increment, and changes in quality of life. The quality of the treatment provided will be assessed by blind calibrated examiners at follow-up, 12 months after treatment, using established criteria for determining ART restorations [34]. Clinical status of the teeth will be assessed using International Caries Detection and Assessment System-II criteria, which span the continuum from sound to extensive decay [35].

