#### Cost Utility Analysis

Cost-utility analysis will be undertaken using scores derived from the CHU_9D [37,38], the EQ-5D-Y, and the new oral health specific utility scale developed in this study. The use of scores from the CHU_9D as outcome measures in child dental health has been suggested [39]. However, in a preliminary evaluation as an outcome measure it was found not to be sensitive to changes in childhood oral health [40], while the use of the adult version of the EQ-5D has been suggested as being able to differentiate oral health states [41]. Hence, we will further test the usefulness of the CHU-9D as an outcome measure for childhood oral health and seek to develop an oral health specific multi-attribute utility instrument within this project.

**Table 1 table1:** Participant involvement in the proposed study.

Timepoint	Intervention group (test)	Delayed intervention group (control)
Baseline	Questionnaire: ECOHIS, CHU_9D, EQ-5D-Y, Dental Utility Scale, dental fear and anxiety of parent and child; Clinical assessment of children; ART-based care	Questionnaire: ECOHIS, CHU_9D, EQ-5D-Y, Dental Utility Scale, dental fear and anxiety of parent and child; clinical assessment of children; standard care
1 month after baseline treatment	Questionnaire: ECOHIS, CHU_9D, EQ-5D-Y, Dental Utility Scale; child dental fear and anxiety	Questionnaire: ECOHIS, CHU_9D, EQ-5D-Y, Dental Utility Scale; child dental fear and anxiety
6 months after baseline treatment	ART-based care; focus group interviews	Standard care; focus group interviews
12 months after baseline treatment	Questionnaire: ECOHIS, CHU_9D, EQ-5D-Y, Dental Utility Scale; child dental fear and anxiety; clinical assessment	Questionnaire: ECOHIS, CHU_9D, EQ-5D-Y, Dental Utility Scale; child dental fear and anxiety; clinical assessment; ART-based care

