### Treatment Procedures

Test children will be provided with care by dental therapists previously trained in and using the ART approach. Treatment will be undertaken at SDS clinics or field settings, using portable equipment. Restorative treatments will be provided using hand instruments principally, without the use of local anesthesia with the cavity prepared and subsequently restored with a glass-ionomer cement. Where extractions are required, the procedure will be undertaken using standard care approaches. All children will also be provided with preventive fluoride varnish applications at treatment and reviewed at 6-month follow-ups. All treatment will be recorded in patient clinic records. At the 6-month reviews, participants will be provided with preventive fluoride varnish and any other necessary care. Children unable to be provided with care will be referred for specialist care. There will be no direct costs incurred by the participants for the primary care.

Control children will be provided with standard care as part of the fluoride varnish program. Children found to require dental treatment will be referred for care through the prevailing care pathway, that is, government dental services or local private practitioners.

In order to ensure all participants are offered the opportunity to access dental treatment, and in keeping with the delayed treatment intervention design, control participants will be offered treatment using the test treatment approach after the 12-month follow-up.

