### Sample Size

A recently completed pilot study in WA, which compared ART-based care against standard care, reported a nine-fold difference in the proportion of children referred for specialist pediatric dentist care (5% vs 49%). A conservative difference in effect size of 2.5 was assumed to estimate the sample size (10% vs 25%). The intracluster correlation was estimated from the dental caries experience of Aboriginal children participating in a NHMRC Project Grant (1010758)‒funded cluster randomized trial (.05). Using these parameters, with 15 clusters available in each arm of the trial, the estimated sample size required, at 80% power and alpha of .05, was 165 in each arm of the trial with 11 children per cluster. Allowing for loss to follow-up of 25%, the estimated sample size is 220 per arm of the study or 15 children per cluster. The recently completed pilot trial in WA, undertaken by author PA, achieved 90% retention of study participants after 12 months, while an oral health promotion intervention undertaken by author LJ among an Aboriginal population achieved 80% retention of study participants. The estimated sample size will have sufficient power to detect a 33% difference in mean ECOHIS at 90% power and alpha of .05.

The study timeline is shown in Table 2. It is expected that community engagement will take the bulk of the first year in recognition of the challenges of undertaking research in northwestern WA, which is as far as Sydney is from Perth (about 3000 km). Participant recruitment and treatment provision is similarly expected to take up to 2 years because of constraints of locations of communities and weather conditions.

**Table 2 table2:** Study timeline, indicated by actions taken per quarter.

Action	Year 1				Year 2				Year 3				Year 4				Year 5			
	1	2	3	4	1	2	3	4	1	2	3	4	1	2	3	4	1	2	3	4
Community engagement, staff recruitment, training, ethics approval, printing	✓	✓	✓	✓																
Participant recruitment, baseline, examinations, randomization, commence treatment, baseline data entry			✓	✓	✓	✓	✓	✓	✓	✓										
Follow-up examinations, focus group interviews, delayed intervention group treatments							✓	✓	✓	✓	✓	✓	✓	✓	✓					
Data entry, data clean-up, data analyses									✓	✓	✓	✓	✓	✓	✓	✓	✓			
Report preparation, community presentation and feedback																	✓	✓	✓	✓

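### The 12-month visit is timed from baseline in one section and from baseline treatment in Table 1, and the one-month questionnaire needs a treatment date that some control children may not have

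*Protocol article*

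**What the plan says.** The Protocol article gives these timings:

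- **Recruitment:** "Study participants will be reviewed after 12 months from baseline". This review comprises a clinical examination and a follow-up questionnaire, for all participants.
- **Table 1 (under Cost Utility Analysis):** the row with the final questionnaire and clinical assessment is labelled "12 months after baseline treatment" in both arms. The baseline row lists ART-based care for test children and standard care for controls.
- **Measures, on restorations:** "The quality of the treatment provided will be assessed by blind calibrated examiners at follow-up, 12 months after treatment". This sentence concerns the quality of the treatment given, not caries increment or quality of life. The same section has every participant examined at the 12-month follow-up.
- **Measures, on the early questionnaire:** "Both test and control groups will complete the same questionnaire on COHRQoL, child dental fear, the CHU_9D, and the EQ-5D-Y, one month after treatment". The Then-test is tied to the same point.
- **Treatment Procedures, on controls:** "Control children will be provided with standard care as part of the fluoride varnish program", and "Children found to require dental treatment will be referred for care through the prevailing care pathway".

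Outcomes names specialist referral and caries increment as primary, and quality of life as secondary.

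**The concern.** Caries increment accumulates with time. If one section starts the clock at baseline and another at treatment, field staff can schedule the visit by either. Under the treatment origin, the interval over which new caries is counted depends on how soon each child was treated, and that process differs by arm. A difference in increment would then partly reflect a difference in observation time.

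The one-month time point raises a separate matter. A questionnaire defined by a treatment date does not exist for a child without one. Control children enter a preventive varnish programme and are referred only if they need treatment. The Introduction (Current Situation) itself warns that children with poor access to services may remain untreated. If treatment means dental treatment, the one-month control group is formed after allocation by need and access. Comparing it with the test arm is not the intention-to-treat contrast promised in Data Analysis. Multiple imputation does not obviously rescue it, since a post-treatment value is undefined for an untreated child.

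**Working it through.** **1. Does any stated figure depend on the time origin?** No. The sample size reproduces without it. Inputs from Sample Size: 10% vs 25%, intracluster correlation 0.05, 15 clusters per arm, 80% power, alpha 0.05 (two-sided assumed).

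- Individually randomized, unpooled variance: (1.960 + 0.842)² × (0.10×0.90 + 0.25×0.75) / 0.15² = 96.8 per arm.
- Clusters needed with m children each, adding one cluster per arm: 1 + 96.8 × [1 + (m − 1)×0.05] / m.
- m = 10 gives 15.04, just over 15. m = 11 gives 14.2, which fits.
- 15 × 11 = 165 per arm, and 165 / 0.75 = 220 per arm, as stated.

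**2. Can the two origins coincide for test children?** Recruitment stratifies communities on caries data from the baseline examination, so allocation follows that examination. Appointments are arranged after it, and Measures allows several visits per child. Some lag between baseline and test treatment is therefore built in. Its length is not given.

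**3. Window under each origin.** Let L_T and L_C be the months from baseline examination to treatment in the test and control arms.

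- Baseline origin: both windows are 12 months, ratio 1.00.
- Treatment origin: ratio = (12 + L_T) / (12 + L_C).

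If the standard care in Table 1's baseline row counts as control treatment, L_C may be 0. With L_C = 0, L_T assumed, and caries accruing evenly:

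| L_T (assumed) | Test window, treatment origin | Ratio to 12-month control window | Test time after treatment, baseline origin |
|---|---|---|---|
| 1 month | 13 months | 13/12 = 1.08 | 11 months |
| 3 months | 15 months | 15/12 = 1.25 | 9 months |
| 6 months | 18 months | 18/12 = 1.50 | 6 months |

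Equal lags remove the difference: with 3 months in each arm, 15/15 = 1.00. A longer control lag reverses it: L_T = 3 and L_C = 6 give 15/18 = 0.83. If treatment means dental treatment, a control child who never has any has no defined window under Table 1's label.

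The last column shows the other side of the conflict. With a baseline origin, test children cannot also have the full 12 months after treatment that Measures gives for restoration quality.

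**4. The one-month questionnaire.** The documents do not give the share of controls with a dental treatment date. Over an assumed range, and using the 165 per arm expected after loss to follow-up:

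- 75%: 0.75 × 165 = 124 controls contribute
- 50%: 0.50 × 165 = 83
- 25%: 0.25 × 165 = 41

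Up to 165 test children would contribute. If control standard care (varnish) counts as treatment, this loss shrinks or disappears, but the control clock may then start at or near baseline while the test clock starts later, as in step 3.

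**The case against.** The best defence is that no section gives the two arms different origins. Recruitment uses baseline for everyone, and Table 1 uses one row label for both arms. Since Table 1 lists care in both arms at baseline, its label may simply mean care started around baseline, which would nearly reconcile it with Recruitment. The participant flow chart (Figure 1) is not shown and may settle the matter.

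Much of this stands. Under Recruitment the windows are equal, and under Table 1 they differ only if lags differ by arm. The defence does not remove the risk, however: if control care starts at baseline while ART waits for examination, allocation and booking, a treatment origin produces unequal windows.

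A reader might infer more than the documents support:

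- **That caries increment and quality of life will be compared over unequal windows.** This is conditional, not established.
- **That the 12-month comparison rests on a selected control subset.** It does not. The examination and the quality-of-life questionnaire at 12 months are planned for all participants.
- **That Measures sets the whole 12-month review from treatment.** That sentence is confined to restoration quality.
- **That a child's lag may be very long because "Participant recruitment and treatment provision is similarly expected to take up to 2 years".** This describes the trial-wide field period, not one child's wait.
- **That the one-month subset biases the cost-utility result.** The article does not say which time points supply the utility difference, and utilities are also collected at baseline and 12 months.

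**Conclusion.** The inconsistency is real and affects the visit that supplies a primary outcome. Recruitment and Table 1 give that visit different time origins, and for test children the two cannot be identical. Bias in caries increment is possible rather than shown: it requires the treatment origin and lags that differ between arms. With a lag in the test arm only and even accrual, the distortion in exposure would be 8%, 25% or 50% at assumed lags of 1, 3 or 6 months. It would count against the test arm, and a longer control lag would act the other way.

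The selection concern is confined to the one-month questionnaire and Then-test, and holds only if treatment there means dental treatment. The sample size is unaffected. The point is worth correcting because scheduling is cheap to settle in advance, whereas an assessment taken at the wrong time cannot be retaken.

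**What to change.** - Reconcile Recruitment, both timing statements in Measures, and the row labels of Table 1.
- Time the 12-month caries and quality-of-life assessments from the baseline examination in both arms, and account for actual follow-up time in the caries increment analysis.
- For any early comparison between arms, time the questionnaire from baseline in both arms. Otherwise, report the one-month post-treatment questionnaire and Then-test descriptively among treated children.
- State what counts as treatment for a control child at the one-month point.
- Assess restoration quality at the same 12-month visit, and record time since treatment.

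**Cost.** This is mostly wording and scheduling. Test children will have somewhat less than 12 months of follow-up after treatment, so restoration quality is judged a little earlier than Measures states. Keeping both a baseline-timed and a post-treatment questionnaire would add a contact for some children, which matters in very remote communities. Choosing only one of the two avoids that.

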### Outcomes

Primary outcomes are specialist referral and the increment in dental caries. Secondary outcomes are quality of life and acceptability of the ART-based care.

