### Aims

The principal aim of the proposed study is to develop, implement, and evaluate a remote primary care model to deliver effective primary dental services, encompassing treatment and preventive services, to Aboriginal preschool children (based on minimally invasive approaches including ART). This will be compared with standard care for cost and benefits in terms of improved dental health and reduced childhood dental anxiety. Our specific aims and hypotheses are:

Aim 1. Measure the proportion of children able to be provided with care without the need for dental specialist referral and the increment in dental caries. Hypothesis: The proportion of children successfully managed without specialist referral and without new dental caries will be higher in the test group compared with the control.

Aim 2. Develop a dental-specific health utility scale and measure the change in childhood health utility. Hypothesis: The change in health utility will be greater in the test group compared with the control.

Aim 3. Undertake an economic evaluation of the intervention. Hypothesis: The test intervention will have either less costs with greater/similar health gain or affordable incremental costs for additional unit of health outcomes.

Aim 4. Measure the change in childhood oral health-related quality of life. Hypothesis: The child oral health-related quality of life in the test group will be better than the control

Aim 5. Evaluate the acceptability of the ART-based care through focus group interviews. Hypothesis: The ART-based care will have greater acceptability than the control.

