### Data Analysis

Data will be analyzed on an intention-to-treat (ie, participants analyzed on the basis of their group allocation regardless of whether they received the intended treatment), and per protocol basis (participants analyzed on the basis of their group allocation and receiving the intended treatment). Descriptive statistics will be presented and baseline variables will be compared between groups to test for fairness with respect to the randomization. Aim one (primary outcome) will be tested using test of proportions and logistic regression to control for potentially confounding factors. Changes in health utility and COHRQoL (secondary outcomes) will be tested using paired (within group) and unpaired (between groups) and parametric and nonparametric tests as appropriate, and multivariate analysis using linear regression for continuous variables and Poisson regression for count variables to control for possible intergroup imbalances. Responsiveness of the COHRQoL scale will be determined by calculation of effect sizes for the scale overall and specific domains. Statistical significance will be set at alpha=.05. All analyses will take into account the cluster design and will incorporate multilevel analyses where indicated. Multiple imputation of missing data will be further undertaken to evaluate its impact on the primary and secondary outcomes.

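### The primary endpoint is given as two outcomes in one place and as one composite proportion in another; only referral is sized, and no rule says what makes the trial positive

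*Protocol article*

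**What the plan says.** Four places in the protocol article bear on the primary endpoint.

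- **Outcomes** names two: "Primary outcomes are specialist referral and the increment in dental caries". One is yes/no, the other an increment.
- **Aims, Aim 1** measures the same two things: "Measure the proportion of children able to be provided with care without the need for dental specialist referral and the increment in dental caries". Its hypothesis, however, is about one proportion: "The proportion of children successfully managed without specialist referral and without new dental caries will be higher in the test group".
- **Data Analysis** uses the singular and names binary methods only: "Aim one (primary outcome) will be tested using test of proportions and logistic regression to control for potentially confounding factors". Linear regression and Poisson regression appear in the next sentence, which concerns health utility and quality of life and labels them secondary. One general level is given: "Statistical significance will be set at alpha=.05". No split, order or both-required rule accompanies it.
- **Sample Size** uses referral proportions of 10% and 25%. It gives no caries rate, standard deviation or effect.

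**The concern.** These statements cannot all be followed. An analyst working from Outcomes would test referral and a caries increment separately. An analyst working from the Aim 1 hypothesis would test one composite proportion. The binary methods in Data Analysis suit the composite, or referral alone, but leave a count or mean increment with no named model.

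The same data could then lead to different conclusions. With a clear referral benefit and no caries benefit, the trial is positive if either outcome suffices and negative if both are required. On the composite it could well be missed. If the choice is made after the data are seen, it will look data-driven whichever way it goes. The error rate and the power also depend on which section is followed.

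**Working it through.** **1. Reproduce the stated sample size.** Inputs from Sample Size: 10% vs 25% referred, intracluster correlation 0.05, 15 clusters per arm, 80% power, alpha .05. Two-sided testing is assumed, since the text does not say.

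- Individually randomised, pooled-variance formula: n = [1.96·√(2p̄(1−p̄)) + 0.8416·√(p₁(1−p₁)+p₂(1−p₂))]² / (p₁−p₂)², with p̄ = 0.175. This gives 99.5, so 100 per arm.
- Clusters needed with m children each, with the usual one extra cluster: 1 + 100·[1+(m−1)·0.05]/m. At m = 10 this is 15.5, more than the 15 available. At m = 11 it is 14.6, which fits. So 15 × 11 = 165 per arm.
- Loss of 25%: 165/0.75 = 220, and 220/15 = 14.7, so 15 per cluster.

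Both stated figures reproduce from referral alone. Neither the increment nor the composite enters them.

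**2. Type I error by reading.**

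- Composite as the one primary outcome: one test, 5%.
- Both outcomes required: at most 5%.
- Either suffices, each at .05, independent: 1 − 0.95² = 9.75%. With correlated test statistics (bivariate normal) it is 9.1% at correlation 0.5 and 7.8% at 0.8.

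**3. Power for referral.** Design effect 1 + (11−1)·0.05 = 1.5, so the effective n is 165/1.5 = 110 per arm. By normal approximation, power is 83.8% at .05 and 75.8% at .025.

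**4. Power for the composite.** The document gives no caries rate, so these shares are assumptions. Non-referral is 90% vs 75% (from 10% vs 25% referred), multiplied by an assumed caries-free share in each arm, with referral and caries taken as independent and the intracluster correlation kept at 0.05. Same approximation, effective n 110 per arm:

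| Caries-free, test vs control | Composite, test vs control | Power |
|---|---|---|
| 30% vs 30% | 27.0% vs 22.5% | 12% |
| 50% vs 50% | 45.0% vs 37.5% | 20% |
| 70% vs 70% | 63.0% vs 52.5% | 35% |
| 55% vs 50% | 49.5% vs 37.5% | 43% |
| 60% vs 50% | 54.0% vs 37.5% | 69% |
| 65% vs 50% | 58.5% vs 37.5% | 88% |
| 45% vs 30% | 40.5% vs 22.5% | 82% |
| 80% vs 70% | 72.0% vs 52.5% | 85% |

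The first three rows assume no effect on caries; the others assume one. Power for the increment itself cannot be worked out even this far, because no mean, spread or effect is given.

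**The case against.** The strongest defence is that the sections can nearly be made to agree. The Aim 1 hypothesis may be shorthand for two parallel hypotheses, and the measurement sentence of Aim 1 matches the Outcomes section. A multiplicity rule is also something that a condensed article may leave to an analysis plan. That stands in part: the missing rule alone would be a weak point. But an analysis plan can add a rule only once it is clear which endpoint the rule applies to, and here the printed sections point to different endpoints.

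A reader might infer four stronger things, which the document does not support.

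- *That there are three definitions.* There are two: the pair in Outcomes and the composite in the Aim 1 hypothesis. Sizing the trial on referral does not define a third.
- *That each outcome is tested at .05, so the error rate is 9.75%.* The text gives one general significance level. The 9.75% needs an either-suffices rule, which is not stated, and independent outcomes.
- *That the named tests cannot handle caries.* They fit caries as the Aim 1 hypothesis puts it, new disease or none. They fail only for a count or mean increment.
- *That the composite has far less power than 80%.* The figure of about 20% assumes no caries effect, contrary to what Aim 1 expects. With a large effect, power exceeds 80%.

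**Conclusion.** The conflict is in the printed text and needs correcting. Outcomes and the Aim 1 hypothesis describe different primary endpoints, and Data Analysis names no model for a primary caries increment. The success criterion is therefore ambiguous.

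Depending on the section followed, type I error lies between at most 5% and 9.75%. The 165 and 220 per arm, and the 80% power, are sound for referral under the plan's own inputs and two-sided testing, and carry over to nothing else. Composite power depends wholly on assumed caries-free shares and on independence, so the range shown illustrates the uncertainty and is not an estimate of a shortfall.

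**What to change.** Reconcile Aims, Outcomes and Data Analysis before 12-month outcomes are known. The Results section says that recruitment is still in progress.

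**Simplest resolution.** Make specialist referral, the only outcome sized, the single primary outcome at two-sided .05. Make caries increment the first secondary outcome, tested only if referral is significant, and analyse it with a count model that accounts for clustering. Reword the Aim 1 hypothesis to match, or label the composite exploratory. The sample size of 165/220 per arm then stands. The cost is wording in three sections, and caries increment loses a primary status for which no power is stated.

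**If both outcomes stay primary.** State the decision rule, name a model that fits the increment, and say that the stated 80% power covers referral only.

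- *Both required:* alpha needs no adjustment, but power for caries should be shown.
- *Alpha split at .025:* referral power at 165 per arm falls from about 84% to 76%. Keeping 80% needs 121 per arm before clustering. That is 13 per cluster without the extra-cluster allowance (195 evaluable, 195/0.75 = 260 recruited per arm) or 15 per cluster with it (225 evaluable, 225/0.75 = 300 recruited).

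**If the composite is intended.** Name it as the single primary outcome in Outcomes, and give the caries rates and effect on which its power rests.
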